## Abstract

**Background:**

Platelet-rich plasma (PRP) is an autologous platelet concentrate. It is prepared by separating the platelet fraction of whole blood from patients and mixing it with an agent to activate the platelets. In a clinical setting, PRP may be reapplied to the patient to improve and hasten the healing of tissue. The therapeutic effect is based on the presence of growth factors stored in the platelets. Current evidence in orthopedics shows that PRP applications can be used to accelerate bone and soft tissue regeneration following tendon injuries and arthroplasty. Outcomes include decreased inflammation, reduced blood loss and post-treatment pain relief. Recent shoulder research indicates there is poor vascularization present in the area around tendinopathies and this possibly prevents full healing capacity post surgery (*Am J Sports Med***36**(6):1171–1178, 2008). Although it is becoming popular in other areas of orthopedics there is little evidence regarding the use of PRP for shoulder pathologies. The application of PRP may help to revascularize the area and consequently promote tendon healing. Such evidence highlights an opportunity to explore the efficacy of PRP use during arthroscopic shoulder surgery for rotator cuff pathologies.

**Methods/Design:**

PARot is a single center, blinded superiority-type randomized controlled trial assessing the clinical outcomes of PRP applications in patients who undergo shoulder surgery for rotator cuff disease. Patients will be randomized to one of the following treatment groups: arthroscopic subacromial decompression surgery or arthroscopic subacromial decompression surgery with application of PRP.

The study will run for 3 years and aims to randomize 40 patients. Recruitment will be for 24 months with final follow-up at 1 year post surgery. The third year will also involve collation and analysis of the data. This study will be funded through the NIHR Biomedical Research Unit at the Oxford University Hospitals NHS Trust.

**Trial registration:**

Current Controlled Trials: ISRCTN10464365

## Background

Platelet-rich plasma (PRP) is an autologous platelet concentrate. It is derived from patients’ own blood and mixed with an agent to activate platelet formation. PRP works by increasing the number of platelets, which release growth factors to help healing of a particular area [1]. Oral surgeons have used PRP for many years and it is now being widely used in orthopedic interventions. Studies have included comparisons of PRP injections with a steroid or analgesic injection or comparing PRP application during surgery with no PRP application.

Current clinical evidence suggests PRP could have beneficial effects on hard and soft tissue healing due to the presence of growth factors stored in the platelets [2]. The evidence also shows that PRP applications can be used to accelerate bone and soft tissue regeneration following tendon injuries and arthroplasty. Outcomes include decreased inflammation, reduced blood loss and post-treatment pain relief [3]. Previous studies assessing the use of PRP in orthopedics have involved plantar fasciitis, lateral epicondylitis, Achilles tendonitis and arthroplasty. However, there is little evidence regarding the use of PRP in shoulder pathologies.

Shoulder tendinopathies, such as rotator cuff impingement and tears, are an increasing problem in orthopedic practice and reportedly account for up to 70% of shoulder pain problems [4]. Impingement is the most frequent cause of shoulder pain in the general population. The term ‘rotator cuff tear’ refers to structural failure and tissue disruption in at least one of the four muscles and tendons that form the rotator cuff. Any tear that involves rotator cuff disruption that does not extend all the way through the tendon is termed a partial-thickness tear (PTT). PTTs are more prevalent than full-thickness tears [5]. Information is also lacking regarding the risk of progression of PTTs to full-thickness tears.

Impingement and rotator cuff tears are associated with progressive change in the shape of the acromion, with spurs forming at its anteroinferior margin. These spurs are thought to narrow the subacromial space, thereby making physical contact more likely, particularly in certain positions of the arm (for example, the painful arc) [4,6] and resulting in inflammation, pain and potentially some loss of function.

A high proportion of patients with impingement and partial-thickness tears will respond to conservative treatment [7]. The most common surgical intervention for impingement and partial-thickness tears is arthroscopic subacromial decompression (SAD). Indications for surgery include persistent and severe pain combined with functional restrictions that are resistant to conservative measures. Despite surgery being considered at this point, some reports show that surgery is no more effective than physiotherapy in the relief of pain when used in patients at this stage [8,9]. Recent studies indicate the poor vascularization present in the area around tendinopathies possibly prevents full healing capacity [10]. The application of PRP may help to revascularize the area and consequently promote tendon healing. Such evidence highlights an opportunity to explore the efficacy of PRP use in subacromial decompression surgery for rotator cuff pathologies.

The objective is to assess the effectiveness of treating subacromial impingement syndrome and partial-thickness rotator cuff tears with autologous platelet-rich plasma. We plan to compare the outcome of standard arthroscopic subacromial decompression surgery with the outcome of the same surgery plus the administration of autologous platelet-rich plasma.

## Methods/design

PARot is a parallel blinded superiority-type randomized controlled trial. The two groups are: arthroscopic subacromial decompression surgery and arthroscopic subacromial decompression surgery with application of PRP.

The study will run for 3 years. Recruitment will be for 24 months with final follow-up at 1 year post surgery. The final year will involve collation and analysis of the data. Only patients will be blinded as to whether they received PRP or not.

Patients identified for the study will have failed conservative treatment for their shoulder impingement or partial-thickness tear and will be listed for subacromial decompression surgery. Conservative treatment may include physiotherapy and injections of steroid and or local anesthetic. The routine step following failed conservative treatment would usually involve being put on the waiting list for surgery (SAD).

Patients will be identified in, and recruited from, the shoulder outpatient clinics at the Nuffield Orthopaedic Centre, Oxford University Hospitals (OUH) NHS Trust, Oxford. Diagnosis of shoulder impingement or partial-thickness tear will be confirmed with ultrasound in the clinic and the patient will be put on the waiting list for surgery. A surgical member of the research team will introduce the trial to the patient and refer them to a research nurse for recruitment.

Informed consent procedures, baseline assessments (including the Oxford shoulder score) and randomization are performed up to 3 days prior to surgery due to organizational requirements in relation to operating schedules and required equipment. Randomization is undertaken using sealed envelopes based on a simple computer-generated randomization list.

Routine perioperative care will proceed and the patient will have their operation as planned.

As randomization occurs very close to the point of treatment, patients will be followed up in clinic at 6 weeks and at 3 and 6 months post treatment. Patients will be blinded to the treatment they are allocated to. Assessors and surgeons are unable to be blinded in this instance. All patients will remain on the waiting list for surgery as per standard care and may have their surgery at the planned date. A summary of the study design is portrayed in the flow chart (Figure 1).

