**Figure 1 F1:**
[figure not shown]
**Study flow chart.** PROMS, patient-reported outcome measures.

PARot study assessments will include patient-reported outcome measures (PROMs), histological examinations, functional assessments and patient satisfaction and health economic questions. Evaluation of routine basic blood tests will also be included in the PARot assessments. A full blood count (taken as part of routine preoperative assessment and not a study intervention) will indicate the presence of clotting substances and any PRP contraindications the patient may have.

Patients will be required to attend a clinic appointment for assessments at 6 weeks and at 3 and 6 months post treatment. A postal questionnaire (containing the Oxford shoulder score, Oxford satisfaction index and EQ 5D) will also be sent out at 12 months post treatment. Clinical assessments and any adverse reactions or side effects can be documented. Table 1 outlines the outcome measures and their correlating time points.

**Table 1 T1:** Outcome assessments

	**Baseline**	**6 weeks**	**3 months**	**6 months**	**12 months**
**Oxford shoulder score**	X	X	X	X	X
**Tissue biopsy**	X^a^		X^b^		
**Pain diary**		X			
**Clinical examination**	X	X	X	X	
**Oxford satisfaction index**	X	X	X	X	X
**EQ 5D**	X	X	X	X	X
**Complications**	X	X	X	X	X
**Venous blood sampling**	X				
**Ultrasound**	X		X	X	

^a^ Ultrasound-guided biopsy during surgery.

^b^ Ultrasound-guided biopsy at follow-up visit.

The primary outcome measures are the Oxford shoulder score (OSS) assessed at 12 months and the histological assessments of the biopsy tissue. The Oxford shoulder score is a condition-specific questionnaire providing a total score based on the patient’s subjective assessment of pain and activities of daily living (ADL) impairment. The range of available scores is 0 (worst) to 48 (best) [11]. The score is reliable and valid. The questionnaire will be administered to patients at the baseline and during their follow-up visits.

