Secondary outcomes involve basic histological tests to assess vascularity, antibodies and neural tissue and cell creation [12]. Tissue samples will be taken at the baseline (during surgery) and again 3 months later. Secondary outcomes also include radiological and clinical assessment of impingement syndrome to assess the progression of any cuff tear. Data related to patient satisfaction and resource use involved in each treatment arm will also be collected at the baseline and again at follow-up visits.

The PARot study will include patients diagnosed with subacromial impingement syndrome or a partial-thickness tear who have failed conservative treatment. The inclusion criteria are the following:

• Patients with shoulder impingement syndrome or a partial-thickness rotator cuff tear.

• Diagnosis confirmed using ultrasound scan by a trained member of the research team.

• Failed conservative treatment.

• Listed for arthroscopic subacromial decompression surgery.

• Male or female, aged 35 to 75 years old.

Patients may not enter the study if any of the following apply:

• Full thickness rotator cuff tears.

• Participants with a history of significant trauma. (fracture, dislocation, instability and so on), surgery, osteoarthritis or other significant pathology of the affected shoulder not related to the rotator cuff.

• Patient is unable to consent.

• No conservative treatment.

• Previous surgery on affected surgery.

• Contraindications to PRP (listed below).

PRP contraindications:

• History of diabetes mellitus.

• Platelet abnormality or platelet count <100 × 10^9^/l.

• Hematological disorder.

• Serum hemoglobin <11 g/dl.

• Use of systemic cortisone.

• Use of any anticoagulant.

• Evidence of gangrene, ulcers or peripheral vascular disease.

• History of hepatic or renal impairment or dialysis.

• Patient is known to have a psychological, developmental, physical, emotional or social disorder that may interfere with compliance with study requirements.

• History of alcohol or drug abuse.

• Patient has a religious or cultural conflict with the use of platelet gel or blood products.

• Patient has inadequate venous access for blood draw.

• Patient is currently receiving or has received radiation or chemotherapy within the last 3 months prior to the study.

• Female participants who are pregnant, lactating or planning pregnancy during the course of the study.

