### Tendon biopsies

Tendon biopsies for histological assessments will be taken during surgery for both groups of patients. This will involve a small amount of tendon tissue (the size of a small grain of rice) excised using a 14G core biopsy needle under ultrasound guidance. This will be taken in a sterile manner as part of the surgical procedure before the application of the PRP.

A further biopsy will be taken from both groups of patients during their 3-month follow-up visit. This biopsy will be taken using an ultrasound guidance technique and a biopsy needle in exactly the same manner as performed at surgery, under sterile conditions. Local anesthetic will be infiltrated around the area of the biopsy to numb the region before the tissue sample is taken. This technique has been successfully trialed and used in previous studies conducted by this research group (ethics ref: 09/H0605/111 and 09/0605/78).

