### The Oxford shoulder score

The OSS at 12 months is the primary outcome measure and the primary hypothesis is based upon this evaluation. The design is a simple two-group cross-sectional comparison. The data will be first checked for normality using histograms and Shapiro–Wilk tests. Independent *t*-tests (assuming normal distribution and equal variance) will then be performed to test the hypothesis that there is no difference in the mean OSS between the two groups. The null hypothesis will be rejected for significance set at α = 0.05.

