### Histology assessments

The tendon structure will be examined with basic histology by staining specimens with hematoxylin and eosin, toluidine blue and Congo red. Immunohistochemical analysis will also be performed using specific antibody markers such as vascular endothelial markers (CD 34), macrophage-associated markers (CD 68) [12] as well as neural tissue (S100) and cell proliferation (PCNA). Statistical analysis with *t*-tests will be used with significance set at α = 0.05.

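### The blanket statement that assessors cannot be blinded makes no exception for histology, although coded slides would remove a possible detection bias in an outcome that is named primary and formally tested

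*Protocol article*

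**What the plan says.** On blinding, Methods/design in the protocol article says "Only patients will be blinded as to whether they received PRP or not" and later "Assessors and surgeons are unable to be blinded in this instance". Neither sentence separates the clinic from the reading of tissue.

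On the standing of histology, the text after Table 1 says "The primary outcome measures are the Oxford shoulder score (OSS) assessed at 12 months and the histological assessments of the biopsy tissue". Shortly afterwards the outcome list says "Secondary outcomes involve basic histological tests to assess vascularity, antibodies and neural tissue and cell creation". The section on the Oxford shoulder score says "The OSS at 12 months is the primary outcome measure and the primary hypothesis is based upon this evaluation".

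On the tissue itself, "Tissue samples will be taken at the baseline (during surgery) and again 3 months later". Of the sample at surgery, the Tendon biopsies section says "This will be taken in a sterile manner as part of the surgical procedure before the application of the PRP". The same section has both arms biopsied at both times, with the same technique.

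On the reading and analysis, the Histology assessments section says "The tendon structure will be examined with basic histology by staining specimens with hematoxylin and eosin, toluidine blue and Congo red". It adds immunohistochemistry for four kinds of marker (vascular, macrophage, neural, proliferation) and then t-tests at a 0.05 level. It does not say who reads the slides, whether they are masked, or which values enter the t-tests.

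**The concern.** A surgeon who applies PRP cannot be blinded, and a clinic assessor may be hard to mask. Neither reason carries over to a stained section, which shows no allocation unless its label does. Taken literally, the two blinding sentences nevertheless put the slide reader in the same group.

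The Background rests the case for PRP on revascularization and tendon healing. Vascular staining and tendon structure are the direct look at that mechanism, and a reader who knows the arm also knows which direction is hoped for. If scoring involves judgement, that knowledge can move the scores in one arm. Several stains and markers are to be read, so the exposure recurs. At stake is whether a histological difference between arms could be taken at face value. The trial takes trouble to keep patients blind, down to a single venepuncture site in both arms, so an open reading of slides would be out of keeping with its own care.

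**Working it through.** **1. Does anything in the document prevent masked reading?**

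- Baseline sample: both arms, at surgery, before PRP is applied (Tendon biopsies).
- 3-month sample: both arms, same ultrasound-guided needle technique (Tendon biopsies).
- Readout: stained sections and antibody markers (Histology assessments).

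Sampling does not differ between the arms, and no stated step requires the reader to know the allocation. Coding is therefore feasible on the facts given.

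**2. The plan's own figure.** The only sample size is for the OSS (Statistics and analysis): SD 3, difference 3, power 0.8, alpha 0.05, 17 per arm, raised to 20 for losses (34/40 = 85%, so a 15% allowance).

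- Normal approximation: 2 × (1.960 + 0.842)² × (3/3)² = 15.7, so 16 per arm.
- Noncentral t, two-sided: 16.71, so 17 per arm, with power 0.807 at 17.

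The stated 17 reproduces. It is not a count of evaluable biopsies and is borrowed below only as a plausible size.

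**3. Illustration of reader bias (assumed inputs).** Suppose there is no true effect and an unmasked reader shifts one arm's scores by b SD. The two-sided t-test with n per arm has 2n − 2 degrees of freedom and noncentrality b × √(n/2). The false-positive rate is the probability that |t| exceeds its critical value (2.037 at n = 17, 2.024 at n = 20).

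| Assumed shift b (SD) | Noncentrality, n = 17 | False-positive rate, n = 17 | False-positive rate, n = 20 |
|---|---|---|---|
| 0 | 0 | 5% | 5% |
| 0.1 | 0.292 | 5.9% | 6.1% |
| 0.2 | 0.583 | 8.7% | 9.5% |
| 0.25 | 0.729 | 10.9% | 12.0% |
| 0.5 | 1.458 | 29.3% | 33.8% |

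These rates are per marker. A larger sample makes them worse, because the shift is systematic. A shift that depended only on time point would fall on both arms alike and cancel, so knowledge of the arm is what does the harm.

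**4. What the baseline biopsy could add (assumed correlation r between baseline and 3 months).** With 3-month values alone, the difference detectable with 80% power at 17 per arm is 0.99 SD. ANCOVA multiplies the SD by √(1 − r²), and change scores multiply it by √(2(1 − r)). The one degree of freedom spent on the covariate is ignored.

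| r | Variance removed by ANCOVA | Detectable difference, ANCOVA | Detectable difference, change score |
|---|---|---|---|
| 0.3 | 9% | 0.99 × 0.954 = 0.95 SD | 0.99 × 1.183 = 1.17 SD |
| 0.5 | 25% | 0.99 × 0.866 = 0.86 SD | 0.99 × 1.000 = 0.99 SD |
| 0.7 | 49% | 0.99 × 0.714 = 0.71 SD | 0.99 × 0.775 = 0.77 SD |

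Over this range ANCOVA is better than either form of t-test, and a change score is worse than 3-month values alone when r is below 0.5.

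**The case against.** The strongest reply is that the sentence on assessors follows the description of clinic visits and pairs assessors with surgeons, so it may mean clinic assessors only. A condensed article may also leave slide handling to the full protocol. This stands in part: the article does not establish that slides are, or will be, read open. But the other sentence confines blinding to patients without qualification, and taken together the two amount to a stated rule that reaches histology. They are not mere silence on a detail.

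Several further objections stand in full:

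- A reader might infer that the trial's main result is exposed. It is not. The primary hypothesis and the sample size rest on the 12-month OSS, which blinded patients complete by post.
- A reader might infer that the analysis throws the baseline biopsy away. The article does not say so. It names only t-tests, and a t-test on change would use the baseline. The cross-sectional wording concerns the OSS, and full analysis detail is deferred to the statistical analysis plan. An unadjusted t-test between randomized arms is also valid, so adjustment is a gain in precision and not the repair of an error.
- The article identifies no reader, no place of reading and no method of scoring. How much judgement enters is therefore inferred, and whether a suitable unaware reader is at hand is unknown.
- The false-positive rates follow from chosen shifts and a borrowed sample size. They do not show that a bias of that size exists.

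**Conclusion.** The point holds for histology only. As worded, the article's blinding rule covers the reading of an outcome that it calls primary in one place and secondary in another, and that it tests formally under either label. Nothing shown prevents masked reading, so the possible detection bias is avoidable.

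Its size cannot be taken from the documents. The range of about 11% to 29% false positives per marker, against a nominal 5%, assumes a reader shift of 0.25 to 0.5 SD, no true effect and 17 evaluable patients per arm. With a shift of 0.1 SD the rate would be 5.9%. The feasibility argument does not depend on any of these figures.

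This is a change that should be made, but it does not threaten the OSS comparison.

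**What to change.** - **Wording.** Restrict the statement that blinding is impossible to surgeons and to those clinic assessors who cannot be masked. State that histology is read masked.
- **Procedure.** Label slides with a random code that hides patient, arm and time point. Score baseline and 3-month slides together in random order. Break the code only after the scores are locked.
- **If slides have already been scored openly.** The Trial status section reports completed follow-up on 40 patients, so this is possible. Recode and re-read the retained slides masked, and report that the earlier scoring was open. A reader who remembers the slides would not be fully masked, so someone without that exposure is preferable where available.
- **Analysis, as an optional gain.** Compare the arms on each 3-month marker by ANCOVA with the pre-PRP biopsy value as covariate, and say so in the statistical analysis plan. If the plan already specifies how the baseline enters, no more than a check is needed.

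The cost is a code list, labelling time, a few sentences of text and possibly a second reading. No additional patient, visit or biopsy is required.

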### Subacromial decompression surgery

Subacromial decompression surgery is performed under general anesthetic. The procedure involves insertion of an arthroscope into the glenohumeral joint where the joint surface is inspected along with the intra-articular portion of the long head of the biceps and the joint surface of the rotator cuff tendons. Once this has been performed the arthroscope is removed and inserted into the subacromial bursa, which lies outside the rotator cuff tendons and beneath the acromion process of the scapula. In the bursa, the acromion and superior surface of the rotator cuff are assessed to ensure the coracoacromial ligament and the Acromioclavicular (AC) joint remains intact. The projecting under surface of the distal part of the acromion is resected. The intervention is considered to be a well-established and well-documented procedure. Patients with full cuff tears noted at the time of surgery will not be eligible and will be excluded from the trial at operation.

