### Subacromial decompression surgery with autologous platelet-rich plasma

This group will receive the same operation as described above plus an autologous platelet-rich plasma concentrate injection into the rotator cuff tendon during surgery. PRP can be applied by a variety of methods: as a gel, as an injection, as a sutured film during surgery, sprayed directly onto repaired tissue or injected subcutaneously. This study proposes the use of a gel sprayed directly onto the decompression area.

Specific preparation techniques will be stipulated by the company providing the PRP device. Described below is a guideline for the preparation involved in administering PRP, which was taken from the protocol of the PATH study (REC Reference: 09/H0605/78), also run in this department.

PRP is prepared using a sterile technique in the theatre. First, 50 ml of venous blood will be withdrawn from the patient into a syringe. The syringe will be attached to the selective platelet separator device and the blood is transferred into the device. The device will separate platelets and remove red blood cells and white blood cells. The result is 5 ml to 6 ml of platelet-rich concentrate (PRC), which will be collected in an attached syringe [13].

The 5-ml syringe containing the concentrate is attached via a dual injection kit to another syringe containing bovine thrombin (200 units) and 1 ml of 10% calcium chloride (activator). The dual syringes are used to inject the PRC into the subacromial space.

Reviews in oral surgery recommend that the derivation of PRP must be a sterile process. Platelets must not be lysed or damaged in any way, as damaged platelets may not release their growth factors. Studies that suggest there is no benefit to PRP application may have suffered from poor preparation of the PRP solution [14]. It is therefore important to send excess PRP to the laboratory for platelet analyses and quality assessment [15]. Data obtained from tendon tissue samples from all patients will also provide valuable information regarding the integrity of the tendon including any effects PRP may have on this.

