### Venous blood sampling

A sample of 18 ml of venous blood will be obtained from the patient for analysis and inclusion in the Oxford Musculoskeletal BioBank project (ethics ref: 09/H606/11). The sample will be taken prior to commencement of surgery once the patient is anesthetized. For those patients in the PRP group this sample will be taken using the same needle as for the blood taken for making up the PRP solution. In this way patients will be blinded to their group allocation as both groups will have a single venepuncture site and the sampling volume will be unknown to the patient as they will have been anesthetized prior to venepuncture.

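### Assessors are declared impossible to blind without a reason, which leaves biopsy histology and ultrasound readings open to detection bias that coded reading would avoid

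*Protocol article*

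**What the plan says.** Methods/design sets the blinding rule in two sentences: "Only patients will be blinded as to whether they received PRP or not", and later "Assessors and surgeons are unable to be blinded in this instance". Neither sentence, nor anything else in the article, says why assessors are grouped with surgeons.

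The same section and Table 1 list the outcomes that someone other than the patient must judge:

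- **Histology** of tendon biopsies taken at surgery and at 3 months. Methods/design names it as a primary outcome alongside the 12-month OSS, and Histology assessments plans t-tests at 0.05.
- **Ultrasound** at baseline, 3 and 6 months, and **clinical examination** at baseline, 6 weeks, 3 and 6 months. The stated secondary purpose is "radiological and clinical assessment of impingement syndrome to assess the progression of any cuff tear". Secondary outcome measures confines the secondary endpoints to description.

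The OSS is a patient-reported score. At 12 months it arrives in a postal questionnaire.

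**The concern.** A surgeon who applies PRP knows the arm, and no design can change that. A person who reads a slide or an ultrasound image need not know it. If readers do know the arm, judgements about vascularity, cell markers or tear progression can drift towards what they expect, and the two arms are then no longer measured in the same way. For histology this would feed directly into a significance test. For ultrasound it would distort the descriptive summaries from which the authors still hope to see a sign of effect. Declaring blinding impossible closes off a simple safeguard.

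**Working it through.** The article gives no figure for this point, and no arithmetic decides it. The check is whether anything it describes would disclose the arm to a reader who was not told it.

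**Step 1: what differs between the arms, and where.**

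- Anaesthesia: "Subacromial decompression surgery is performed under general anesthetic" (Subacromial decompression surgery). This applies to both arms.
- Operation: the PRP arm has the same procedure, "plus an autologous platelet-rich plasma concentrate injection into the rotator cuff tendon during surgery". The same section also describes other ways of applying the product, but each takes place during the operation.
- Preparation: "PRP is prepared using a sterile technique in the theatre".
- Blood sampling: "In this way patients will be blinded to their group allocation as both groups will have a single venepuncture site" (Venous blood sampling). The sample is drawn once the patient is anaesthetised.
- Biopsies: Tendon biopsies has both arms biopsied at surgery, before any PRP, and again at 3 months by the same technique.

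The described difference is therefore confined to theatre. No extra scar, puncture, visit or biopsy marks the PRP arm at follow-up.

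**Step 2: which outcomes knowledge of the arm can reach.**

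| Outcome | Judged by | Planned analysis | Route for bias |
|---|---|---|---|
| Biopsy histology | slide reader | t-tests at 0.05 | direct |
| Ultrasound, tear progression | image reader | descriptive | direct |
| Clinical examination | examiner | descriptive | direct |
| OSS at 12 months | patient, by post | t-test at 0.05 | only if the patient learns the arm |

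The status of histology is not uniform in the article. Methods/design names it as primary and then lists basic histological tests among the secondary outcomes. Its own analysis section plans tests all the same, so it is the reader-judged outcome with most at stake.

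**Step 3: can the direct routes be closed?** Slides can carry a code that hides both arm and time point. Stored ultrasound images can carry a code too. Neither step requires the reader to meet the patient, so neither depends on who was in theatre or who attends clinic. Clinical examination is different: it needs a person in the room, and the article does not say whether an uninformed examiner is available.

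**Step 4: does the rule as written already allow this?** It does not. The article does not define who counts as an assessor, but a rule that blinds patients only leaves slide and image readers unblinded.

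**The case against.** **The primary score is barely touched.** The 12-month OSS is self-completed and posted, six months after the last clinic visit (12 − 6 = 6). No assessor scores it, and Venous blood sampling sets out a specific measure to keep patients unaware. This stands. A reader might infer that unblinded staff undermine the primary test, and could illustrate it. With the plan's SD of 3 and 17 per arm, an assumed bias of 1 point gives a noncentrality of 1 / (3 × √(2/17)) = 0.97 and a two-sided false-positive rate of about 16% instead of 5%. The result moves with the assumption: 0.5 points gives about 7.6% and 1.5 points about 29%. The documents supply no such shift and do not suggest that staff disclose the arm, so these figures do not measure a defect in this plan.

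**Staff outside theatre may need to know the arm.** Consent, baseline assessment and randomisation take place up to 3 days before surgery, partly because of equipment. Research staff who see patients later may therefore know the allocation. This also stands. It cannot be claimed that only the theatre team need know, or that an uninformed examiner certainly exists. It does not affect coded reading.

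**Ultrasound and clinical outcomes carry no formal test.** This is true, and it limits the consequence to biased description. It does not apply to histology.

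**The article is condensed and admits the limitation.** A reason may exist in a fuller protocol. But the article does more than stay silent: it states that blinding is impossible, and its own procedures do not bear that out for readers of coded material.

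**Conclusion.** The point holds for outcomes judged by a reader. The article states that assessors cannot be blinded, gives no reason, and describes nothing that would reveal the arm to someone reading coded slides or images. Histology matters most because it is named as primary and is tested at 0.05. Ultrasound matters less because it is only described. Clinical examination is exposed too, but whether it can be masked depends on staffing that the article does not describe.

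The size of the bias cannot be given. The OSS is at most indirectly exposed, and the sample size is not affected. The conclusion assumes that slides and images can be labelled without identifying the arm, and that ultrasound images are stored, which the article does not say. It is a point the sponsor should act on. It does not show that the OSS comparison is invalid.

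**What to change.** Replace the sentence on assessors and surgeons in Methods/design, and bring the patients-only sentence into line with it:

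> Surgeons cannot be blinded. Biopsy slides and saved ultrasound images are labelled with a code and read by existing team members without knowledge of allocation and, for slides, of time point. Where feasible, clinical examination is done by an existing team member who was not in theatre and has not been told the allocation; otherwise it is reported as unblinded. For patients still in follow-up, the 12-month postal questionnaire asks the patient to guess the allocation.

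If masked reading is truly not possible, state the reason instead.

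The cost is the coding and batch reading, and one extra question. No treatment, visit or sample size changes. Two limits apply. Coded ultrasound reading works only if images were kept. And Trial status reports completed follow-up on 40 patients, which equals the planned total of 20 per arm, so changes to examinations or questionnaires cannot help those patients. Coded reading of slides and of any stored images can still cover them.
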